**Lay abstract**

How can we reduce the impact of the COVID-19 pandemic on children's mental health? We propose the *Open Sky School*, a nature-based intervention applied in the school setting. Currently, there is increasing enthusiasm for outdoor education in schools, especially since the onset of the COVID-19 pandemic. Could such nature-based interventions have salutogenic effects? Experimental studies conducted worldwide show that contact with nature (e.g., urban park or forest) improves mental health. Preliminary results suggest that this is also the case for children when they come into contact with nature during school hours. However, no experimental studies have tested the benefits of spending time in nature at school as a strategy for improving children's mental health.

To fill the gaps in the existing literature, we will conduct a clustered randomized controlled trial to test the effectiveness of the *Open Sky School* program. The *Open Sky School* is a nature-based intervention applied in the school setting to promote students' and teachers' mental health. The intervention will span 12 weeks, two hours per week. We will recruit 80 to 100 5th and 6th grade elementary school classes from schools in Quebec. The intervention will include mental health promotion activities in and through nature (e.g., cooperation, compassion/empathy, mindfulness) and nature-based educational activities. We will evaluate the effectiveness of this intervention on children's mental health. The results could help decision makers implement education programs involving contact with nature to promote mental health. Our results could provide empirical evidence of such practices that come at little cost and have a high potential for deployment at the population level.

# **Research Ethics Board Approved Protocol for the Open Sky School: Effectiveness of a nature based intervention in the school setting on improving mental health and healthy habits among children**

## **1. Overview and impact**

Good mental health during childhood paves the way for good physical and mental health throughout life. Before the pandemic, 1 in 3 children experienced emotional and/or internalized and/or externalized behavioral problems, such as anxiety, depression, inattention/hyperactivity, and opposition. However, since the COVID-19 pandemic, the number of emergency room visits and prescriptions for medication for mental health problems in young people has increased significantly in Quebec compared to previous years, and particularly among children from disadvantaged backgrounds. In addition to school closures and distance learning, many children experienced the impact of parental stress, as well as a marked decrease in social contact with friends and family. To mitigate the pandemic's negative impact on children's mental health, it is crucial to identify and implement feasible interventions that effectively improve mental wellbeing.

Scientific studies with experimental and quasi-experimental designs conducted around the world, including by our team, show that contact with nature (e.g., walking in a nearby park versus in the city) improves adults' mental health, by reducing depression, anxiety, suicidal ideation and inattention. As such, a growing number of initiatives have emerged encouraging individuals to spend time in nature to improve their mental health, including during the COVID-19 pandemic. This enthusiasm is echoed in the education sector, where a growing—though still limited—number of teachers are incorporating outdoor education with aims similar to nature-based interventions used in therapeutic contexts. However, the impact of time spent in nature on children's mental health remains inadequately understood, largely due to a scarcity of experimental studies.

This research project will help fill this gap by testing the benefits of time spent in nature, in the school setting, on mental health symptoms of 5th and 6th grade elementary school students in Quebec. We will conduct a clustered randomized controlled trial to test the effectiveness of a 12-week intervention, called the *Open Sky School*, which will be implemented by teachers. The *Open Sky School* consists of 24 hours of time spent in nature (i.e., nearby park or other natural green environment such as a waterfront or forest) during school hours. The students will be exposed to nature two hours per week for a period of 12 weeks, from March to June 2023. The waitlist control group will be composed of students in classes continuing usual teaching practices from March to June 2023. The control group will have access to the intervention, including 10 mental health activities accessible on a [website](#), in the fall of 2023. Teachers in the experimental group will have access to training and coaching during the intervention period to facilitate the integration of mental health and pedagogical activities into the regular school curriculum. This will help facilitate teachers' implementation of the intervention.

Outdoor education involving contact with nature is rapidly gaining interest in school settings, but the actual potential of these initiatives to promote young people's mental health is poorly understood. Therefore, it is vital to generate evidence to guide decisions about which types of mental health promotion interventions we should prioritize in schools, as well as the appropriateness/relevance of such initiatives. In addition, given the current post-pandemic context and the increased risk of infection in children under 12, time spent in nature outside at school is a promising strategy to reduce the risk of viral exposure and thus help keep schools open during the 2022-2023 academic year, while reducing the risk of spreading COVID-19 and other infections in children. Our results will help provide decision-makers with the evidence needed to decide which outdoor education programs to implement in a post-pandemic context. The evidence generated can then be mobilized on a wider scale, across the province and even the country.

## **2. Current state of knowledge: justifying nature-based intervention in schools to improve children's mental health**

Our research team is primarily interested in the benefits of time spent in nature on children's mental health, at the population level. However, we are also concerned with implementing an intervention that can realistically and seamlessly be integrated within the school setting. This will enhance the relevance of the intervention. Additionally we will focus on integrating pedagogical activities to better fit teachers' needs. Thus, by combining these two approaches, we can ensure that we will promote better mental health while implementing an intervention that enables teachers to comply with the cycle 3 (5th and 6th grade) Quebec school curriculum. The following is a summary of the existing literature on 1) the therapeutic and salutogenic impacts of contact with nature on mental health, and 2) outdoor education in primary schools.

### **2.1. What do we know about the effects of contact with nature on mental health?**

First, observational studies examining the associations between exposure to nature (measured by the vegetation index surrounding the place of residence) during childhood and mental health in adulthood report associations between greater presence of green vegetation density and lower levels of depression, anxiety and suicide. In children, some observational studies show that a greater amount of vegetation in the neighbourhood is associated with fewer depressive symptoms, anxiety, and inattention/hyperactivity, while also providing more opportunities for physical activity. Our own preliminary results on a birth cohort of children born in Quebec in 97/98 demonstrated that children living in an urban neighbourhood with a high vegetation index had fewer symptoms of inattention and hyperactivity/impulsivity during adolescence than those who grew up in a less green neighbourhood, and that these associations held after controlling for household and neighborhood socioeconomic status. Second, intervention studies carried out among adults reveal benefits of contact with nature in reducing symptoms of depression and anxiety. For instance, a systematic review of 12 interventional studies based on quasi-experimental design showed that walking in natural environments (e.g., parks) reduced anxiety symptoms in adults more than walking in urban city settings. In addition, a meta-analysis of 16 studies evaluating the effects of an intervention based on spending time in the forest showed reductions in anxiety symptoms. In all, there is evidence of benefits of spending time in nature on mental health, whether the natural space is a forest or an urban park.

However, few intervention studies, most of which are quasi-experimental, have documented the effects of a nature exposure among children. Furthermore, such studies carried out among children targeted those with pre-existing mental health problems. For example, a double-blind, controlled, within-subject study was carried out among children aged 7 to 12 years with a diagnosis of ADHD. The study suggested that 20-minute walks in urban parks reduced concentration problems among participants more than walks in urban environments, such as streets in their neighborhood. Notably, the effect sizes observed were large (0.52 to 0.77) and comparable to the effects of medication. Despite these encouraging results, these findings are emerging and limited. In addition, there is a lack of strong evidence to demonstrate the beneficial impact of contact with nature on children's mental health. This project therefore aims to generate knowledge to document the effects of exposure to nature on the mental health of children attending schools in Quebec in the aftermath of the COVID-19 pandemic.

### **2.2. Explanatory mechanisms**

Although knowledge does not allow us to identify the bio-psycho-social mechanisms involved in the relationship between contact with nature and mental health, some explanations have been put forward: (1) natural spaces can reduce stress (e.g., cortisol) and increase attentional capacities, self-control and problem-solving skills, which in turn promote a restoration of psychological wellbeing;

(2) contact with nature can contribute to improving psychosocial adaptation and mental health by means of increasing physical activity and social connections; and (3) natural spaces have lower exposure to air and noise pollution which is associated with mental health benefits in the short and long term.

### 2.3. What do we know about the effects of outdoor education on children's mental health?

Traditionally, studies examining the impact of outdoor education have primarily focused on educational attainment in various subjects rather than on youth mental health. While positive effects have been observed on physical activity, social skills, and self-esteem, the benefits to mental health remain largely unexplored. It should be noted that outdoor education includes any form of teaching and learning that takes place outside the walls of the school, regardless of the presence of natural spaces. Nevertheless, despite these limitations and the lack of empirical evidence generated from randomized controlled trials, there are a few quasi-experimental studies that have documented the effects of outdoor education on children's mental health. For example, a first study conducted in Sweden carried out among children aged 6 to 12 years used a non-equivalent quasi-experimental design to test if an outdoor education program (e.g., schoolyard) intervention (n=121) reduced mental health symptoms compared to teaching as usual (n=109). The intervention was carried out daily, 1 hour per day for 6 months during which students learned the classic core subjects outdoors by manipulating elements of nature (e.g., branches and stones used to represent mathematical concepts as opposed to textbook content). Findings suggested that the intervention significantly reduced internalizing and externalizing symptoms, but only among boys. Subsequently, a second quasi-experimental study aimed to assess the potential benefits of outdoor education on the mental health of children aged 9 to 11 (n=631) in comparison to teaching as usual. Results suggested that the intervention increased prosocial behaviors among all children and reduced hyperactivity and peer problems, but only among children from underprivileged backgrounds.

### 2.4. Added value of our study

In light of the available results and the previously identified gaps, we propose to implement a clustered randomized controlled trial of an intervention combining both the component of contact with natural spaces and outdoor education. We will evaluate the impact of the intervention on the mental health of 5th and 6th grade elementary students.

## 3. Study objectives

*The primary objective* is to test the benefits of time spent in nature on the mental health of 5th and 6th grade elementary students. To be eligible, students must be aged 10-12 years and attend a school with access to a natural space (i.e., park) within a 1 kilometer radius. We hypothesize that students exposed to our 12-week intervention in the 2022-2023 school year will have fewer internalizing (e.g., depression, anxiety) and externalizing (e.g., opposition, inattention/hyperactivity/impulsivity) symptoms and social problems (e.g., bullying/victimization) compared to children in the waitlist control group, who will follow teaching practices as usual. The *secondary objectives* are to study the intervention's effectiveness on children's nature connectedness and other indicators of students' and teachers' wellbeing. Finally, the exploratory objectives of the project are to assess if the effects of the intervention are maintained in the medium-term (i.e., 3 months later) and to examine potential moderating effects, according to various characteristics of (a) the child, i.e., sex, the presence or absence of a diagnosed mental health disorder in the student's file; and (b) the school, e.g., the geographical area, and the vegetation index of greenness surrounding the school.

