The main component of the *Open Sky School* consists of exposing children to nature. The nature exposure embeds various activities (academic and mental health components), while providing teacher training and support. To this end, we designed an online toolkit of pedagogical and mental health activities that can be conducted outdoors. The mental health activities are rooted in positive psychology (mindfulness, philosophy for children and art therapy) and are designed to improve children's mental health. The pedagogical activities (French language, mathematics and sciences) are aligned on the core academic competencies required by the Ministry of Education of Québec. Teachers will also be allowed to use their own pedagogical activities (if they do, they will be asked to describe their activities), but are encouraged to use those provided in the toolkit, because they were professionally designed and positively appraised in the quality assessment phase. Nevertheless, as our trial primarily aims to reduce mental health problems among children, teachers will be asked to carry out at least 10 mental health activities provided in the toolkit. The toolkit also includes brief video-based modules on best practices and tips for implementing mental health activities outdoors (i.e., how to deal with negative emotions; how children can remain mindful in a noisy environment). Our experts and graduate students in education and clinical psychology will provide teachers with up to 1 hour per week of virtual optional consultation during the intervention to discuss any arising issues related to the intervention and its implementation. Licensed psychologists from the research team will offer psychological support to any participant who reports high levels of psychological distress and reorientate them to appropriate services if needed.

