## **7. Implementation of the intervention (fidelity)**

The teachers will fill out an online logbook in which they will indicate information about each nature visit. They will provide information on the activities they chose to carry out (from our toolkit or others of their choice), the duration of these activities, where the activity was carried out and the total time spent outdoors. They will record if they watched our training videos, if they encountered any problems and the amount of time they spent with our supervisors. This information will be used to evaluate the adequacy of the implementation of our intervention. To fully comply with implementation, there must be of a total of 24 h of intervention (2 h per week for 12 weeks) and a minimum of 10 mental health activities from the toolkit must be carried out. Classes that do not achieve a minimum of 80% completion and comply with content 90% of the time will be excluded from sensitivity analyses. Information contained in the logbooks will be evaluated independently by two researchers and we will analyze inter-rater agreement to ensure the consistency of the codification of the information provided.

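### The primary objective names time spent in nature, but the two-arm contrast tests the whole Open Sky School package and cannot isolate nature

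*Protocol*

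**What the plan says.** **The aim.** Protocol Section 3 states that the primary objective "is to test the benefits of time spent in nature on the mental health of" 5th and 6th grade students. Section 1 describes the project as "testing the benefits of time spent in nature, in the school setting, on mental health symptoms of" the same pupils. The last sentence of Section 2.1 likewise says that the project will document what exposure to nature does for children's mental health.

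**The intervention arm.** Section 6.2 gives 2 hours per week outdoors for 12 weeks, which is 24 hours. It calls nature exposure the main component and then describes other elements. One is a set of psychological activities: "The mental health activities are rooted in positive psychology (mindfulness, philosophy for children and art therapy"), described as "designed to improve children's mental health". On their number it says that "teachers will be asked to carry out at least 10 mental health activities provided in the toolkit". There are also outdoor pedagogical activities, training videos, and optional virtual consultation for teachers of up to 1 hour per week. Section 7 makes the activities a condition of full compliance: besides the 24 hours, "a minimum of 10 mental health activities from the toolkit must be carried out".

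**The control arm.** Section 1 says: "The waitlist control group will be composed of students in classes continuing usual teaching practices", from March to June 2023. Under Section 6.3, controls receive an unguided version, or for former 6th graders a set of mental-health activities, about six months after the start.

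**The hypothesis.** Section 3 words it differently from the objective: "We hypothesize that students exposed to our 12-week intervention in the 2022-2023 school year will have fewer internalizing" and externalizing symptoms and social problems than waitlist controls.

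**The concern.** A two-arm trial estimates the effect of everything that is assigned differently between its arms. Here that includes a set of psychological activities that the protocol itself expects to act on the primary outcome, as well as outdoor teaching and teacher support. The objective names only one of these elements.

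The primary objective sets the claim that the trial may make. If the result is positive and is reported against the objective as worded, it will read as evidence that time in nature improves mental health. The same result could arise mainly from the mindfulness, philosophy or art activities, from the change in teaching, or from a combination. The protocol intends the findings to inform decisions about school programmes. A school that took the objective at its word might adopt park visits and leave out a part that mattered.

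**Working it through.** No arithmetic applies. The question is what the randomised contrast identifies, and it is settled by comparing the stated aim with the content of each arm.

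**Assigned content from T1 (March 2023) to T2 (June 2023)**

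| Element | Intervention | Control | Source |
|---|---|---|---|
| Nature visits, 2 h × 12 weeks = 24 h | Assigned | Not assigned | Sections 1, 6.2 |
| At least 10 toolkit mental-health activities | Assigned, and needed for full compliance | Not assigned | Sections 6.2, 7 |
| Outdoor pedagogical activities (toolkit or teacher's own) | Offered | Not assigned | Section 6.2 |
| Training videos; optional consultation, up to 1 h per week | Offered | Not offered until later | Sections 6.2, 6.3 |

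**What is estimated.** Write *N* for nature exposure, *A* for the mental-health activities, *P* for outdoor pedagogy and *S* for teacher support, with 1 for assigned and 0 for usual practice. The T2 contrast estimates

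E[Y(N=1, A=1, P=1, S=1)] − E[Y(N=0, A=0, P=0, S=0)].

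An effect of nature needs one of two other contrasts:

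- nature alone against usual practice: E[Y(1,0,0,0)] − E[Y(0,0,0,0)]; or
- nature with the rest held fixed: E[Y(1,1,1,1)] − E[Y(0,1,1,1)].

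The first needs an arm with nature visits only, the second an arm with the same activities and support indoors. Sections 4.1 and 4.2 provide two arms, allocated 1:1, and neither of these is among them. More schools make the joint effect more precise but do not separate its parts. The power statement in Section 8 therefore has no bearing on this point.

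**Are the extra elements incidental?** The protocol's text says not. Section 6.2 justifies the minimum of 10 activities by the trial's aim of reducing mental-health problems. Section 7 means that even a fully compliant class never receives nature alone. Section 6.3 gives former 6th-grade controls adapted activities to do by themselves, which suggests that the activities can be separated from the class visits. Section 2.3 describes outdoor education as something that can take place without natural surroundings, so outdoor teaching is a further element distinct from nature.

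**Could other planned data separate them?** The vegetation index (Sections 3 and 5.3) and the logbook (Section 7) vary between schools or classes for reasons that are not randomised. They can describe, but they cannot identify the nature component.

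**The case against.** The best reply is that the protocol mostly does describe a package. The lay abstract speaks of testing a programme that includes mental-health promotion activities. Section 2.4 describes a combination of natural spaces and outdoor education. Section 4.1 defines the nature intervention so broadly that learning and mental-health activities fall within it. The hypothesis in Section 3 concerns the 12-week intervention against usual teaching. Testing a multicomponent programme against usual practice is a legitimate design.

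All of that stands, and it limits the point to the wording of the aim and of any conclusion drawn to it. It does not remove the mismatch. The objective and the hypothesis in the same section ask different questions. The broad definition in Section 4.1 would count an effect of mindfulness as an effect of nature by definition, while Section 6.2 keeps the two apart.

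A reader might also infer more than the documents support:

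- **That a share of the intervention, or of its effect, can be put down to the activities** by dividing 10 by the number of visits. No section says that activities are spread one per visit, 10 is a minimum, and a share of visits does not measure a share of effect.
- **That controls have no outdoor time or never get the activities.** Nothing bars control teachers from outdoor teaching, and Section 1 notes that some teachers already practise it. The difference is in what is assigned, up to T2. Six months from the March 13 start of visits is about September 13, just before the T3 window of September 18 to 23, so controls may have begun by then.
- **That the activities would work as well indoors.** The lay abstract sets them in nature. That they would also work indoors is plausible but not stated.
- **That the sponsor plans to report nature alone to decision-makers.** The statements about decision-makers in the lay abstract and Section 1 concern programmes, and no such planned conclusion appears.

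**Conclusion.** The primary objective is wrong as written. The trial can validly test the Open Sky School package against usual teaching on children's mental health at T2. It cannot test the benefit of time spent in nature as such, because two arms that differ in several elements do not identify the contribution of one of them, whatever the sample size. No numerical size can be attached: the documents give nothing from which the nature share could be derived.

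It would go too far to say that the design is invalid or that the hypothesis cannot be answered; the documents support neither. The conclusion assumes only that the arms receive what Sections 1, 6.2 and 6.3 assign to them up to T2.

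**What to change.** - **Section 3:** restate the primary objective as estimating the effect of the Open Sky School programme (nature exposure plus mental-health and pedagogical activities plus teacher support) on students' mental health, compared with usual teaching.
- **Section 1 and the end of Section 2.1:** change the matching sentences in the same way.
- **Planned conclusion:** word it for the programme, and state that the trial does not isolate nature exposure.
- **Logbook data:** label any analysis by hours outdoors or number of activities as non-randomised exploration.

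The cost is a narrower headline claim. Arms, outcomes, sample size and data collection do not change. Isolating nature would take a further arm, such as the same activities and support indoors; that would be a different trial and is not needed for the programme question.
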